# Risks to Subjects*

- 1. Risks to subjects is no greater than risks associated with general activity in children with SMA. These include the child becoming tired or fussy, bone fracture, sore muscles, and tired head or neck which may result in airway occlusion. Families are required to provide constant adult supervision to mitigate this last risk.
  2. Risks associated with equipment use include: the child falling if not placed in the harness correctly, entanglement due to BWSS misuse or equipment malfunction. When used properly, there are no reports of BWSS causing harm to a child or adult when used as indicated.

# Potential Benefits to Subjects*

- 1. Subjects may experience a new way of moving and interacting with family members and peers. Use of BWSS may increase frequency of motor skill practice and facilitate motor skill development.

# Data Management* and Confidentiality

- 1. Baseline and Final visit assessment scores will be compared. We will explore factors that may impact outcomes including reported frequency of use. Subjects may be stratified into groups based on such factors and sample group change averages will be compared.
  2. All source form data will be stored in locked cabinets in a locked office for the duration of the study. Electronic data entry will be stored on secured NCH research drive ([name]) and will be password protected.
  3. Data will be stored indefinitely
  4. Access to data: only investigators listed on IRB will be provided access to study materials.

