# Study Summary

| **Study Title** | Exploring the feasibility and utility of in-home body weight support harness system use in children treated for spinal muscular atrophy |
| --- | --- |
| **Study Design** | Pilot interventional study |
| **Primary Objective** | Investigate whether BWSS is a feasible option for in-home exercise and investigate the use of home-based functional exercise using a body weight support harness system (BWSS) on motor performance in children treated for spinal muscular atrophy |
| **Secondary Objective(s)** | Explore influence of frequency of use on change in motor performance over 6 months. |
| **Research Intervention(s)/ Investigational Agent(s)** | Enliten, LLC portable body weight support harness system (BWSS) |
| **IND/IDE #** |  |
| **Study Population** | Children who have been treated for spinal muscular atrophy |
| **Sample Size** | Up to 50 children |
| **Study Duration for individual participants** | On-going; each child will be followed for six months with possibility of extension. |
| **Study Specific Abbreviations/ Definitions** | BWSS – body weight support harness system  SMA – spinal muscular atrophy |

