# Objectives

- 1. The purpose of the study is to investigate the feasibility and utility of using an in-home body weight support harness system (BWSS) to promote motor performance in children who have been treated for spinal muscular atrophy. Our primary aim is to explore whether BWSS is a feasible modality for in-home use and whether it impacts motor performance. Our secondary aims are to determine whether frequency of BWSS impacts treatment effect.

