- 1. All functional outcome assessments will be video recorded. Parents may also submit video evidence of motor skill attainment within 7 days of any remote study visit, should the child not perform on the date of the assessment due to child’s mood or behavior.
     - Parents will submit video evidence through secured email communication. Submitted videos will be stored on secured NCH research drive, alongside other assessment videos.
  2. FFamilies will be educated on appropriate activities to help engage with their child in the harness.

Each family will receive an Activity Ideas booklet to reference throughout the duration of the study (Appendix F).

- 1. Families will be asked to fill out the Daily Activity Log (Appendix G) each time the harness is used. The log will include information on the duration and frequency of BWSS use, activities completed with child while in BWSS, and any observed changes in child’s motor function
  2. Families may be asked to attach a motion sensor to the harness system.
  3. **Liability Waiver and Legal Agreement**: Families are to review and sign a liability waiver prior to in-home equipment set-up. This documentation to be created by Nationwide Children’s Hospital Corporate Legal Services department and addresses the expectations and responsibilities of the families to maintain the integrity of the BWSS for the duration of the study
  4. **Safety Considerations**
     - **Equipment Inspection**
       - Equipment will be required to pass study team member inspection using the BWSS Inspection Checklist provided by Enliten, LLC. (Appendix A)
       - Equipment safety checks will occur at screening (prior to in-home set up), baseline, and final visit. Photographs or video of in-home set up will be included in safety documentation.
       - It will be required that the BWSS Inspection Check List be completed by the study team member and reviewed and signed-off by the study team member and parent at baseline and final study visit.
     - **Adult Supervision**
       - Families are required to supervise their child while using the BWSS at all times.
     - **Family Training**

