**Confidential Health Information**

1. **Please mark all categories that reflect the nature of health information to be accessed and used as part of this research.**

Demographics (age, gender, educational level)

Diagnosis

Laboratory reports

Radiology reports

Discharge summaries

Procedures/Treatments received

Dates related to course of treatment (admission, surgery, discharge)

Billing information

Names of drugs and/or devices used as part of treatment

Location of treatment

Name of treatment provider

Surgical reports

Other information related to course of treatment

None

1. Please discuss why it is necessary to access and review the health information noted in your response above.

Timing since initiation of treatment may be a factor in subject response to intervention; this will be explored during data analysis.

3.0 Is the health information to be accessed and reviewed the minimal necessary to achieve the goals of this research?  Yes  No

4.0 Will it be necessary to record information of a sensitive nature?  Yes  No

5.0 Do you plan to obtain a federally-issued Certificate of Confidentiality as a means of protecting the confidentiality of the information collected?  Yes  No

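### The only method named for the frequency-of-use aim, an optional comparison of mean change between groups formed on reported use, discards logged information and cannot support the causal wording of that aim

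*Protocol*

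**What the plan says.** The Protocol's analysis text is short and stands under Data Management and Confidentiality. After a comparison of baseline with final scores it says "We will explore factors that may impact outcomes including reported frequency of use", and then "Subjects may be stratified into groups based on such factors and sample group change averages will be compared". No cut-points, covariates or model are given.

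The aim is worded in two ways. The Study Summary has "Explore influence of frequency of use on change in motor performance over 6 months". The Objectives have "Our secondary aims are to determine whether frequency of BWSS impacts treatment effect".

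The exposure comes from a family-kept Daily Activity Log, filled in at each use. Procedures Involved says of it: "The log will include information on the duration and frequency of BWSS use, activities completed with child while in BWSS". The same section says that families are told how often and how long to use the harness, and that the midpoint visit checks compliance with a schedule.

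Confidential Health Information adds: "Timing since initiation of treatment may be a factor in subject response to intervention; this will be explored during data analysis".

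The design is given as "Pilot interventional study" and the sample size as "Up to 50 children". Local Number of Subjects expects 15, and Multi-Site Research says there is a single site.

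**The concern.** There are two separate problems.

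**Lost information.** The log yields a quantitative exposure, such as sessions or minutes per week. Cutting it into groups treats all children within a group as having had the same use. With perhaps 15 children there is little information to spare.

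**Confounding.** Achieved use is observed. The Protocol itself suggests how it could move with prognosis. Risks to Subjects lists tiredness, fussiness and sore muscles. Withdrawal of Subjects mentions outside treatments that may affect use. The log has families note changes in motor function beside use, so perceived response could shape later use. Eligibility sets no age limits and requires only head righting and a delay in standing or walking, so baseline ability may vary widely. If children who use the harness more were also those who would have improved more anyway, a difference in mean change would look like a dose-response.

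At stake is a claim that more use produces more gain, drawn from a comparison that cannot separate use from who the users are.

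**Working it through.** The Protocol gives no alpha, power, SD or correlation, so there is no figure of its own to reproduce. The calculations below show direction and possible size only.

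**Inputs from the Protocol:** n = 15 (expected) and n = 50 (ceiling).

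**Assumptions:** use and change jointly normal; a median split (the Protocol names no cut-point); two-sided alpha 0.05; correlations as listed.

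**Step 1: information kept.** The relative efficiency of a median split of a normal exposure is 2/π = 0.637. Then 15 × 0.637 = 9.5 and 50 × 0.637 = 31.8, so the split is worth about 10 and 32 children.

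**Step 2: power for a true use-change correlation ρ** (20,000 simulated trials).

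| n | ρ | continuous use | median split |
|---|---|---|---|
| 15 | 0.3 | 19% | 13% |
| 15 | 0.5 | 50% | 31% |
| 15 | 0.7 | 88% | 62% |
| 50 | 0.3 | 58% | 40% |
| 50 | 0.5 | 97% | 84% |
| 50 | 0.7 | about 100% | about 100% |

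Normal-approximation check at ρ = 0.5, n = 50: the difference between halves is 2 × 0.5 × √(2/π) = 0.798, the within-group SD is √(1 − 0.25 × 0.637) = 0.917, and the standard error is 0.917 × √(2/25) = 0.259. Power is Φ(0.798/0.259 − 1.96) ≈ 0.87, near the simulated 84%. At n = 15 the approximation gives 39%. It is too generous there because it ignores the t distribution.

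**Step 3: false positives when use has no effect.** One confounder correlates c with both use and change. The induced use-change correlation is c². For c = 0.5 it is 0.25, and the expected difference between halves is 2 × 0.25 × 0.798 = 0.40 SD (simulated: 0.38 to 0.39).

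| n | c | unadjusted split | adjusted continuous |
|---|---|---|---|
| 15 | 0.3 | 6% | 5% |
| 15 | 0.5 | 11% | 5% |
| 15 | 0.7 | 30% | 5% |
| 50 | 0.3 | 8% | 5% |
| 50 | 0.5 | 28% | 5% |
| 50 | 0.7 | 82% | 5% |

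**Step 4: which change does what.** Continuous use *without* adjustment at c = 0.5 gives about 15% (n = 15) and 41% to 42% (n = 50), more than the split. Adjustment removes the false positives. Continuous use recovers the power. The two changes have to be made together.

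**Step 5: price of adjustment at n = 15, ρ = 0.5.** Power is 50% with no covariate, about 47% with one covariate unrelated to use, and about 41% with three. If three covariates each correlate 0.3 with use and add no prediction of their own, it is about 31%, no better than the split.

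**The case against.** The strongest reply is that this is a secondary, exploratory aim of a pilot. Group mean change is an ordinary descriptive summary there, and model form and covariates commonly belong in a statistical analysis plan, which may exist. That stands as far as it goes: absent covariates are not in themselves a fault. But the Protocol does name a method, names no alternative, and in the Objectives asks it to answer a causal question.

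A reader might infer more than the documents support:

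- *That the Protocol commits to an unadjusted split.* Stratification is optional, the factors are plural, and neither a median cut nor a one-factor-at-a-time analysis is written. The median split above is an assumption. If families keep close to a common schedule, use may bunch and 2/π need not apply.
- *That families simply choose how often to use the harness.* They are instructed on frequency and duration, and compliance is checked. The variation is in adherence, which can still be confounded.
- *That time since drug start is overlooked.* It is to be explored. Exploring it as a factor in its own right does not, however, adjust the comparison by use.
- *That confounding with age or ability is shown.* It is plausible, not demonstrated.
- *That grouping causes the confounding.* Step 4 shows that it does not.

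The objection on cost also stands: with 15 children, a model with three covariates can lose the whole power gain.

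**Conclusion.** The point holds in a limited form. The one method named is inefficient for an exposure logged at every use, and without adjustment it is open to confounding by adherence. Whatever an analysis plan may add, it cannot determine whether frequency affects the treatment effect, so the Objectives claim more than the Study Summary and more than the analysis text can deliver.

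The size is not fixed by the documents and rests on the assumptions listed above. With 15 children and weak confounding (0.3), false positives are near nominal at 6%, and lost information is the main harm; even then power is poor either way (19% against 13% at a use-change correlation of 0.3). With enrolment near 50 and stronger confounding, a spurious dose-response becomes the larger risk. The analysis should be changed, but the matter touches a secondary aim and leaves the primary feasibility endpoints unaffected.

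**What to change.** 1. Under Data Management and Confidentiality, state that for each motor scale the final score will be regressed on continuous logged use, adjusted for the baseline score on the same scale, with the slope and its 95% CI reported as an association. With baseline in the model, the slope for use is the same whether the outcome is the final score or the change.
2. If enrolment is near 15, add age and time since start of the disease-modifying agent only as sensitivity analyses. If it is nearer 50, put them in the main model.
3. Keep mean change by usage group for description only.
4. Reword the secondary aim in the Objectives to match the exploratory verb of the Study Summary.

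**Cost.** This is a change of wording. Use and baseline scores are already collected, demographics are taken at screening, and treatment timing is already meant to be examined. The real price is precision at n = 15, as Step 5 shows. That is the reason for a single covariate in the main model at that size, and for reporting an interval rather than resting on a test.

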# Provisions to Monitor the Data to Ensure the Safety of Subjects*

- 1. Should injury occur as a result of BWSS use, PI will be notified immediately and will review the cause and severity of the injury. If necessary, all other subjects will be notified of cause/effect of injury and if determined to be the safest outcome, study will be terminated and all equipment will be returned to site.

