# Procedures Involved*

- 1. This is a voluntary study investigating the feasibility and effects of a home-based functional exercise program using a body weight support harness system (BWSS) on motor performance in children treated for spinal muscular atrophy. Subjects will be provided with one portable BWSS, manufactured by Enliten LLC, to be used in their home for a period of 6 months. Subjects will engage in a BWSS use and document frequency / duration of use.
  2. **Screening/Baseline**: Subject demographic information and equipment safety check will be completed prior to the initial in-home visit. Baseline assessment of motor function may be completed at any time within a 3 week window prior to or during the initial in-home visit.

**Initial Visit (in-home):** A study team member will travel to the subject’s home to complete the BWSS set up. The BWSS Inspection Check List will be reviewed and signed by the responsible participating family member and the study team member. Pictures or video of the final set-up will be taken and stored in the subjects file. The participating family members will be trained on how to securely strap their child into the harness and on appropriate activities to engage in with their child while in the harness. They will be instructed on frequency and duration of treatment time and asked to document this information in the Daily Activity Log. They may be asked to attach an activity monitor to the harness.

Prior to completion of this visit, the following documentation will be completed: 1) Informed Consent; 2) BWSS Inspection Check List; 3) Pictures or video of BWSS set-up in home.

A study team member will contact the family between the baseline and midpoint assessment visit to ensure the family is comfortable with BWSS use. If the family has questions or concerns, they will be addressed by the study team member via Skype or video conference phone call. If determined necessary by the PI, a study team member will travel to the family’s home for an additional in-home visit.

**Midpoint Assessment Visit**: A study team member will complete functional outcome assessments and evaluate compliance with usage schedule. Daily Activity Log will be checked and completion will be documented.

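### The one stated safety rule notifies the investigator only of injuries caused by the harness system, and no described log item or visit asks about harms, so fractures and near-misses may be under-recorded

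*Protocol*

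**What the plan says.** **Safety rule.** The protocol section Provisions to Monitor the Data to Ensure the Safety of Subjects has a single item: "Should injury occur as a result of BWSS use, PI will be notified immediately and will review the cause and severity of the injury". It goes on to allow that other subjects be told and that the study be terminated. It does not say who links the injury to the device or who notifies the PI.

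**Foreseen harms.** Risks to Subjects, item 1, puts the activity risks no higher than those of general activity in children with SMA and continues: "These include the child becoming tired or fussy, bone fracture, sore muscles, and tired head or neck which may result in airway occlusion". Item 2 adds the equipment risks: "the child falling if not placed in the harness correctly, entanglement due to BWSS misuse or equipment malfunction".

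**Daily Activity Log.** Under Procedures Involved, families complete it "each time the harness is used". Its content is described thus: "The log will include information on the duration and frequency of BWSS use, activities completed with child while in BWSS", together with any change in motor function that the family observes.

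**Scheduled contacts.** Procedures Involved gives the purpose of the between-visit contact: "A study team member will contact the family between the baseline and midpoint assessment visit to ensure the family is comfortable with BWSS use". For the Midpoint visit it says: "A study team member will complete functional outcome assessments and evaluate compliance with usage schedule", and the log is checked for completion. The Final Visit covers functional assessment. Where there is no extension, an equipment check and a log check are added.

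**Endpoints.** Study Endpoints defines feasibility by a survey and documented use. It names no safety endpoint.

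**The concern.** The BWSS is used at home under family supervision, with no study staff present in ordinary use. What the PI learns about harms therefore depends mainly on what families are told to report and what they are asked. The stated rule puts the causal judgement ahead of the PI's own review of cause and is limited to injuries. Nothing described elsewhere makes up for this with a routine question.

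Two things are at stake. The first is the decision to warn other families or end the study, which can rest only on events that reach the PI. The second is how the pilot will be read: at the end, no harms reported could not be told apart from no harms asked about, in a study meant to show whether home use is feasible. This cannot be left to a statistical analysis plan, because an event that was never collected cannot be recovered at analysis.

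**Working it through.** The protocol gives no harm rate, safety threshold or reporting rate, so there is no stated figure to reproduce. The check sets the foreseen events against the stated routes for recording them.

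**1. Which foreseen events meet the notification rule?** The rule has two conditions: there is an injury, and it results from BWSS use.

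| Foreseen event | Injury? | Link to device evident? | Meets the rule as worded? |
| --- | --- | --- | --- |
| Fall or entanglement in the harness, child hurt | yes | yes | yes |
| Fall or entanglement, child not hurt | no | yes | no |
| Equipment malfunction, child not hurt | no | yes | no |
| Airway episode that resolves without injury | no | perhaps | no |
| Fracture evident during a session | yes | probably | probably |
| Fracture noticed later, ascribed to SMA | yes | no | not unless someone links it |

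The last row matters most. Risks to Subjects itself describes fracture as a risk of general activity in SMA, so a family could reasonably ascribe one to the disease.

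**2. Does the log supply what the rule leaves out?** The described items are duration, frequency, activities and observed motor changes, and no harm item is named. The log is completed per session, so an event that appears between sessions has no stated entry point.

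**3. Do the scheduled contacts supply it?** The between-visit contact concerns the family's comfort with use. Midpoint concerns function, compliance and the log, and may be remote. The Final Visit concerns function, with equipment and log checks when there is no extension. In the extension, functional assessments are optional, at intervals of 6-9 months. None is said to include a question on harms.

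**4. How large could the effect be?** It cannot be derived. Purely as an illustration, let p be the proportion of children with a relevant event, c the fraction of those events reported, and n the number of children. The chance that no event is seen is (1 − c·p)^n. The protocol gives n = 15 (Local Number of Subjects) and up to 50 (Study Summary). The values of p (10%, halved and doubled) and c (all or half) are assumptions.

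| p | n = 15, c = 1 | n = 15, c = 0.5 | n = 50, c = 1 | n = 50, c = 0.5 |
| --- | --- | --- | --- | --- |
| 5% | 0.95^15 = 46% | 0.975^15 = 68% | 0.95^50 = 7.7% | 0.975^50 = 28% |
| 10% | 0.90^15 = 21% | 0.95^15 = 46% | 0.90^50 = 0.5% | 0.95^50 = 7.7% |
| 20% | 0.80^15 = 3.5% | 0.90^15 = 21% | 0.80^50 < 0.1% | 0.90^50 = 0.5% |

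The table shows only that, in a study this small, partial reporting can noticeably raise the chance of a clean-looking record. It does not estimate what will happen here, and the point does not depend on it.

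**The case against.** A reader might infer that only device-attributed injuries ever reach the investigator, that the log has no place for harms, and that harms will be under-counted. The protocol supports none of these.

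- The safety item says what happens after a device injury; it does not bar other reports. Withdrawal of Subjects foresees an unrelated injury as a reason to leave and a change in health status as a reason for the PI to withdraw a child. The between-visit contact takes up family concerns. Troubleshooting calls and home visits are provided for, and families are told not to use the system if they have safety concerns. Staff assessing motor function may notice a limb injury.
- The rule is in the passive and leaves cause to the PI. It can be read as asking for any apparent device injury, with causation settled afterwards. An obvious harness injury meets it on its face.
- Appendix G is not shown, and the description of the log need not be exhaustive. A fracture might also surface under observed motor changes. Consent pages, which were removed from the text reviewed, might instruct families on reporting.
- No harm rate is a planned endpoint, so no planned analysis is biased.

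Most of this stands and limits the claim. It does not remove it. The other routes are incidental: none is a stated enquiry about harms, and the withdrawal route misses children who stay in and presupposes the same unreviewed attribution. An instruction to stop use is not an instruction to report. The missing endpoint does not help with the decision to warn families or terminate, which still depends on events being known.

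**Conclusion.** The concern holds in a limited form. The protocol as shown states no systematic collection of harms that is free of prior attribution. Its one notification rule depends on injury and on a link to the BWSS, the log as described names no harm item, and no scheduled contact is said to ask. Near-misses, and fractures ascribed to SMA, may be under-recorded and so may not reach the decision to notify families or terminate.

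The size of any under-count is unknown. The conclusion rests on the protocol's wording and on the log's description matching its form; a harm item in Appendix G would narrow the gap but leave the notification rule as it is. This is an inexpensive improvement worth making, and it does not invalidate the design.

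**What to change.** 1. Reword the safety item so that any injury, fall, entanglement, breathing difficulty or equipment malfunction during or after use is reported to the PI regardless of presumed cause, with the PI then assessing relatedness. State who reports and how.
2. Add a yes/no harm and near-miss line to the Daily Activity Log, if Appendix G lacks one.
3. Ask one standard question about such events at the between-visit contact, the Midpoint visit and the Final Visit.
4. Report the number of children with events descriptively.

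The cost is a wording amendment, one line on an existing form and one question at contacts already planned. The downside is more minor events for the PI to review.
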